## Abstract

**Background:**

Older people account for 25% of all Emergency Department (ED) admissions. This is expected to rise with an ageing demographic. Older people often present to the ED with complex medical needs in the setting of multiple comorbidities. Comprehensive Geriatric Assessment (CGA) has been shown to improve outcomes in an inpatient setting but clear evidence of benefit in the ED setting has not been established. It is not feasible to offer this resource-intensive assessment to all older adults in a timely fashion. Screening tools for frailty have been used to identify those at most risk for adverse outcomes following ED visit. The overall aim of this study is to examine the impact of CGA on the quality, safety and cost-effectiveness of care in an undifferentiated population of frail older people with medical complaints who present to the ED and Acute Medical Assessment Unit.

**Methods:**

This will be a parallel 1:1 allocation randomised control trial. All patients who are ≥ 75 years will be screened for frailty using the Identification of Seniors At Risk (ISAR) tool. Those with a score of ≥ 2 on the ISAR will be randomised. The treatment arm will undergo geriatric medicine team-led CGA in the ED or Acute Medical Assessment Unit whereas the non-treatment arm will undergo usual patient care. A dedicated multidisciplinary team of a specialist geriatric medicine doctor, senior physiotherapist, specialist nurse, pharmacist, senior occupational therapist and senior medical social worker will carry out the assessment, as well as interventions that arise from that assessment. Primary outcomes will be the length of stay in the ED or Acute Medical Assessment Unit. Secondary outcomes will include ED re-attendance, re-hospitalisation, functional decline, quality of life and mortality at 30 days and 180 days. These will be determined by telephone consultation and electronic records by a research nurse blinded to group allocation.

**Ethics and dissemination:**

Ethical approval was obtained from the Health Service Executive (HSE) Mid-Western Regional Hospital Research Ethics Committee (088/2020). Our lay dissemination strategy will be developed in collaboration with our Patient and Public Involvement stakeholder panel of older people at the Ageing Research Centre and we will present our findings in peer-reviewed journals and national and international conferences.

**Trial registration:**

ClinicalTrials.gov NCT04629690. Registered on November 16, 2020

## Administrative information

The order of the items has been modified to group similar items (see http://www.equator-network.org/reporting-guidelines/spirit-2013-statement-defining-standard-protocol-items-for-clinical-trials/).

## Introduction

### Background and rationale {6a}

Ireland like many other countries has seen a steady increase in life expectancy and has an ageing population. By 2031, it is forecasted that there will be more than one million older adults in Ireland, representing an increase from 13% (2015) to 20% of our overall population [1]. According to the United Nations, the population over age 65 in Europe and North America is set to increase by 48% between 2019 and 2050 [2]. International evidence demonstrates that older adults account for up to 25% of all Emergency Department (ED) attendances and experience high rates of adverse outcomes following emergency care such as unscheduled ED return, unplanned hospital admission and functional decline [3, 4]. There is a paucity of research conducted to explore how comprehensive geriatric assessment (CGA) implemented in the ED may improve outcomes among those who present to the hospital for emergency care.

CGA is acknowledged as the gold standard of care for the frail older person [5, 6]. Most studies that examine CGA agree that it consists of a medical, social, functional and psychological review and these constructs determine the overall health of an individual. A comprehensive multifaceted approach, thereby, grants the opportunity to create a synergistic management plan for patients with targeted interventions across these broad domains. A Cochrane review [6] has shown that the use of CGA confers quantifiable and reproducible benefits to the health and wellbeing of older people. The value of CGA in various settings and implementation stages has been established. CGA has been shown to potentially reduce mortality and increase home discharge when performed in dedicated geriatric wards as well as when delivered by mobile geriatric units [6]. It has also been investigated as a treatment model in the surgical inpatient unit setting for elective surgical oncology patients and for those recovering from hip fractures [7]. CGA has been shown to have variable outcome benefits in primary and long-term care settings [8]. A systematic review of five randomised controlled trials by Conroy and colleagues (2011) reported that there was no clear evidence of benefit for CGA interventions among older adults in the ED [9]. Mortality [RR 0.92 (95% CI 0.55–1.52)], readmissions [RR 0.95 (95% CI 0.83–1.08)], subsequent institutionalisation, functional ability, quality-of-life or cognition were not statistically significant in the intervention group. The studies primarily investigated single interventions which were heterogenous in nature [9].

The overall aim of this study is to examine the impact of multicomponent CGA on the quality, safety and cost-effectiveness of care in an undifferentiated population of frail older people with medical complaints who present to the ED and Acute Medical Assessment Unit.

### Objectives {7}

To implement CGA for frail older adults aged 75 years and over, which will be provided by the SOLAR team including a senior geriatric specialist registrar, senior physiotherapist, senior occupational therapist, senior medical social worker and senior pharmacist in the Emergency Department and Acute Medical Assessment Unit (AMAU) in a University teaching hospital.To examine if early assessment and intervention by the SOLAR team improves the quality, safety and cost-effectiveness of care among frail older adults who present to the ED and AMAU.To conduct a process evaluation of the CGA intervention through focus group interviews with the SOLAR team, representatives from the wider ED and AMAU staff along with patient representatives regarding the feasibility, acceptability, and delivery of the intervention.

### Trial design {8}

This study will be a parallel group randomised control trial with a 1:1 allocation ratio. In order to ensure standardised conduct and reporting, the Consolidated Standards of Reporting Trials (CONSORT) guidelines will be used [10].

## Methods: Participants, interventions and outcomes

### Study setting {9}

The study will take place in the ED and AMAU of a University teaching hospital in the West of Ireland. It serves urban and rural areas of Limerick, Clare and North Tipperary. This is a Model 4 university teaching hospital which caters for the general medical, surgical, and emergency treatment of patients with a catchment area of 400,000 people. Model 4 hospitals have a 24/7 ED which function 365 days a year and are tertiary referral centres for the region.

### Eligibility criteria {10}

The inclusion criteria for participants are adults aged ≥75 years with undifferentiated medical complaints. They must be medically stable as deemed by the treating physician. They must have a score of ≥ 2 on the Identification of Seniors at Risk (ISAR) screening tool and present with a medical complaint [11]. Patients will be screened if they present acutely with Manchester Triage Category 2-5 [12]. Patients with the following presenting complaints will be considered for inclusion: limb problems, falls, unwell adult, back pain, urinary problems, chest pain, shortness of breath, abdominal pain and headache. Patients will be screened for inclusion and recruited between 8 am and 4 pm Monday to Thursday. This is based on the availability of the research nurse. Patients outside of these hours will not be recruited. Exclusion criteria include those under the age of 75 years; a score of less than 2 on the ISAR; acute myocardial infarction or stroke; non-medical problems e.g. surgical or psychiatric issues; medically unstable patients; if neither the patient nor carer can communicate in English sufficiently to complete consent or baseline assessment; and confirmed COVID 19 diagnosis or those with symptoms highly suggestive of COVID 19.

### Who will take informed consent? {26a}

Potential participants will initially be informed of the study by the triage nurse or the treating physician. If participants indicate a willingness to hear more about the study, the dedicated research nurse on the project will be informed. The research nurse will subsequently meet with the potential participant, describe the study in detail and provide potential participants with an information leaflet. Participants will be given time to consider the study and to ask questions. Written informed consent will be obtained by the research nurse if/when the participant indicates their willingness to formally participate in the study. Participants will have the duration of their ED or AMAU stay to consider participation in the study. Participants can withdraw at any stage without any negative implications for their treatment.

It is assumed that adults have the capacity to consent or refuse participation unless it is established by the research nurse that they lack capacity. The research nurse will discuss the study with the patient. Where a patient is able to comprehend, retain and explain back what the study entails to the research nurse, believes the information provided and can weigh up the information to make an informed decision, then capacity will be assumed. Where a patient does not demonstrate these abilities, they will be deemed not to have the capacity to consent to research participation and a proxy consent will be obtained from the next of kin with assent from the patient. The next of kin will be allowed time to consider the study and ask questions on behalf of the patient. This consent may be obtained over the phone due to the current hospital visiting restrictions relating to COVID and there will be documentation of whom the consent was obtained from. Should participants choose to drop out of the study, they will undergo routine clinical practice in the ED or AMAU. As this study is a once-off intervention, should participants drop out after the intervention is completed, they will not receive telephone interviews from the research team.

### Additional consent provisions for collection and use of participant data and biological specimens {26b}

There will be no biological specimens collected for the study.

## Interventions

### Explanation for the choice of comparators {6b}

The comparison group will receive usual care as would be current practice in the ED or AMAU. Currently, there is no dedicated team to perform CGA in the ED and AMAU at UHL with ad hoc allied health assessment available only at the discretion of the referring ED doctor or medical team. This process of usual care will be continued during the study and will be documented.

### Criteria for discontinuing or modifying allocated interventions {11b}

CGA is a dynamic process and may change depending on the patient's presentation. Participation in the study is voluntary. Participants will be free to withdraw consent and leave the study at any time without giving a reason and without affecting their care. Should a patient withdraw consent to participate in the study, we will seek clarification on whether withdrawal is from a particular element of the study, for example, participation in the CGA, questionnaire completion or access to healthcare records. Previously collected anonymised data will still be used in the analyses. In cases where participants do not respond to follow-up assessments, outcome data that do not involve participant contact (e.g. data from hospital database) will continue to be collected in these cases.

No formal interim analyses are planned for the primary or secondary outcomes. A single final analysis is planned after the study is closed to recruitment and follow-up and when the full database has been screened, cleaned and prepared for analysis.

### Strategies to improve adherence to interventions {11c}

A number of strategies have been developed to support adherence to the intervention. A detailed protocol has been created and shared with the SOLAR team. Daily briefings/team meetings are planned to troubleshoot queries or concerns by the team. Training on the procedures around participant consent has been conducted. A comprehensive and detailed delegation log has been developed.

### Relevant concomitant care permitted or prohibited during the trial {11d}

Participants will be under the medical care of their treating physician for the duration of their ED or AMAU stay. All relevant consultant stakeholders will continue to provide clinical governance for the patient as per standard clinical practice. Participants who are admitted as an inpatient will be transferred to a relevant ward following their ED or AMAU stay where their medical care will be transferred to the usual medical team and allied health team as required. There is no care which will be prohibited as part of the trial.

### Provisions for post-trial care {30}

Participants who are discharged from the ED or AMAU to the community setting or nursing home will be discharged to the care of their General Practitioner (GP) and will obtain follow-up with a geriatric service in their catchment area if required. The GP will be informed of their participation in the study. Participants may also be referred to community nursing, allied health professionals or community care teams. A detailed letter describing the CGA intervention and assessment will be sent to the GP and other relevant healthcare professionals for all intervention group participants discharged directly from the ED or AMAU. All other patients will have the usual hospital discharge letter provided on discharge.

### Outcomes{12}

The primary outcome of the study is patient ED length of stay or Patient Experience Time (PET) time, which is recorded as time of arrival at the ED until discharge from ED to home or admission to a ward. For participants in the AMAU, this is defined as the time from arrival at the hospital to discharge from AMAU or admission to a medical ward.

Secondary outcomes include mortality, ED revisit, unplanned hospital visit(s) or nursing home admission within 30 days and 6 months of initial index visit. Healthcare utilisation will also be captured at 30 days (GP visit, Public Health Nurse visit, Allied Health Services) by telephone contact. Follow-up at 30 days and 6 months will be captured by telephone contact by a research nurse who is blinded to group allocation. Patient reported outcomes at 30 days include a global measure of function (Barthel Index) and quality of life survey (EuroQoL-5D EQ-5D) [13, 14]. In addition, patient satisfaction with their index visit will be explored using a patient satisfaction questionnaire. A detailed process evaluation will be completed using a mixed methods approach. The process evaluation will explore stakeholders’ experience of implementing the intervention as well as examining factors that enabled or hindered the delivery of same.

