### Sample size {14}

We estimated the sample size based on the primary outcome (ED length of stay) using G*Power version 3.1. Using data from the Patient Experience Time (PET) database employed in the ED at UHL (unpublished data), the average ED length of stay for patients aged 75 and older for the 2019 yearly period was 18.63 h (standard deviation 19.91 h). Estimating a 50% decrease in ED length of stay in the intervention group (mean 9.31 h), and with a 20% attrition rate to follow-up, a sample size of 236 patients (118 in each group) will be required to achieve 90% power with two-tailed tests at an alpha level of 0.05.

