## Assignment of interventions: allocation

### Sequence generation {16a}

Eligible participants will be block randomised in groups of 50 participants using a computer-generated 1:1 allocation through a Sealed Envelope website (www.sealedenvelope.com).

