### Methods in analysis to handle protocol non-adherence and any statistical methods to handle missing data {20c}

An intention to treat analysis using linear mixed models will be used to compare outcomes between the intervention and control arm and account for the correlation within-subject over time, while adjusting for differences in participant characteristics at baseline where appropriate. A sensitivity analysis, via multiple imputation, will be used to explore whether adherence to the intervention influences the effect of the intervention on the primary outcome.

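### The primary outcome pools ED and AMAU stays, but care setting is neither a named stratum nor a prespecified covariate, which gives up some precision at no saving

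*Protocol article*

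**What the plan says.** Under Outcomes {12}, the ED stay is "recorded as time of arrival at the ED until discharge from ED to home or admission to a ward". The same section then covers the second unit: "For participants in the AMAU, this is defined as the time from arrival at the hospital to discharge from AMAU", or to a medical ward if admitted. Both feed a single primary outcome.

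Under Sequence generation {16a}: "Eligible participants will be block randomised in groups of 50 participants using a computer-generated 1:1 allocation". No stratification factor is mentioned.

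Under Statistical methods {20a}, ED length of stay is compared by an independent samples t test, with the Mann-Whitney test for skewed data. Neither takes a covariate. Section {20c} describes an intention-to-treat linear mixed model, "adjusting for differences in participant characteristics at baseline where appropriate". No variable is named. The subgroups in {20b} are discharge location and Clinical Frailty Score, plus control patients seen by another team; ED versus AMAU is not among them.

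**The concern.** An ED and an acute medical assessment unit may well have different typical stays. If they do, part of the spread in the pooled outcome is simply the difference between units. A test that ignores setting leaves that spread in its standard error. A model or stratified test that uses setting removes it.

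The adjustment rule in {20c} does not secure this gain. It is triggered by differences seen in the data, so whether setting enters the model is settled after the fact. It also sits beside unadjusted tests in {20a} for the same outcome. At stake are some precision in the primary comparison and a clear, prespecified view of whether the effect appears in both units.

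**Working it through.** **Inputs from the protocol (Sample size {14}):** ED mean 18.63 h, SD 19.91 h; intervention mean 9.31 h; 118 per arm; 20% attrition; two-sided 5%; 90% power.

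**Inputs that are assumptions:** AMAU share s = 0.20 to 0.50; AMAU mean m = 6 to 9 h; AMAU coefficient of variation equal to the ED value, 19.91/18.63 = 1.069. The documents give none of these.

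**1. The plan's own figure.** A difference of 9.31 h over an SD of 19.91 h gives a t-test requirement of 97.1, so 98 per arm. 98 × 1.2 = 117.6, so 118, as stated. With the difference taken as 18.63 − 9.31 = 9.32 h, power is 94.7% at 118 per arm and 89.4% at 95 per arm (118 × 0.8 = 94.4, rounded up).

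**2. Share of variance due to setting.**

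- Within-setting variance: W = (1 − s) × 19.91² + s × (1.069m)²
- Between-setting variance: B = s(1 − s)(18.63 − m)²
- R² = B/(W + B); adjusting multiplies the standard error by √(1 − R²)

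Example with s = 0.5, m = 6: W = 0.5 × 396.4 + 0.5 × 41.1 = 218.8; B = 0.25 × 12.63² = 39.9; R² = 39.9/258.6 = 15.4%; √(1 − 0.154) = 0.920, a cut of 8.0%.

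Power is for a two-sample t comparison at 118 per arm with a common SD. The difference is half the pooled control mean, and the SD is √(W + B) unadjusted or √W adjusted.

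| s | m (h) | W | B | R² | SE cut | Difference (h) | Power, unadjusted | Power, adjusted |
|---|---|---|---|---|---|---|---|---|
| 0.2 | 9 | 335.6 | 14.8 | 4.2% | 2.1% | 8.35 | 92.7% | 93.7% |
| 0.2 | 6 | 325.4 | 25.5 | 7.3% | 3.7% | 8.05 | 90.8% | 92.7% |
| 0.5 | 9 | 244.5 | 23.2 | 8.7% | 4.4% | 6.91 | 89.8% | 92.2% |
| 0.5 | 6 | 218.8 | 39.9 | 15.4% | 8.0% | 6.16 | 83.4% | 89.0% |

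The gain from adjusting runs from 1.0 to 5.6 points.

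**3. A wider set of assumptions.** Hold the total SD at 19.91 h and the difference at 9.32 h. Let the AMAU share be 10-50% and the gap between unit means D be 3-12 h. Then R² = s(1 − s)D²/19.91² is 0.2-9.1% and the standard error falls by 0.1-4.6%. Power at 118 per arm rises from 94.7% to between 94.8% and 96.4%. If the units differ by only 3 h, the gain is negligible.

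**4. Chance imbalance.** Treating allocation as unstratified, the SD of the between-arm difference in AMAU share is √(2s(1 − s)/118), or 5.2-6.5 percentage points. Multiplying by 1.96 and by (18.63 − m) gives a shift of 0.98-1.61 h. This is already inside the unadjusted interval. For s = 0.5, m = 6 the 95% half-width is 1.96 × 16.08 × √(2/118) = 4.10 h unadjusted and 1.96 × 14.79 × √(2/118) = 3.77 h adjusted, and √(4.10² − 3.77²) = 1.61 h, which is that shift.

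**The case against.** **Validity is not in question.** A reader might infer that a chance excess of AMAU patients in one arm could pass for a treatment effect. The documents do not support that as a flaw in the test. Under 1:1 randomisation the unadjusted comparison is unbiased, and its standard error already carries this imbalance (step 4). The type I error rate is not inflated. This objection stands in full.

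**The power gap has another cause.** A reader might set the 83-93% unadjusted power in the table against 94.7% for ED alone and attribute the gap to leaving setting out. That does not follow. The gap arises because a 50% cut in a shorter pooled mean is a smaller difference in hours. With the 9.32 h target held, the same pooled SDs give 97-99% power. Sizing the trial on ED data alone is a separate point, and a covariate does not repair it.

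**The clocks are closely parallel.** Both run from arrival until the patient goes home or to a ward. The wording differs in start point and unit, so any heterogeneity would come mainly from the units themselves.

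**Covariates are often left to an SAP, which is not shown.** That is fair, so the absence of a covariate list is not the point. The point is what the protocol does fix: unadjusted tests for this outcome, and an adjustment rule driven by observed differences.

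**Setting may not be clear-cut.** The Intervention description {11a} has patients approached after ED triage, and Outcomes {12} does not say how someone who moves from ED to AMAU is classified. Outcomes {12} and Recruitment {15} suggest that setting is known at enrolment. This objection shapes the fix without removing the point.

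**Conclusion.** The point holds as a matter of efficiency and prespecification. The primary outcome combines two settings, no stratum is named, the stated tests are unadjusted, and the adjustment rule is data-driven and does not mention setting. The cost is a standard error about 2-8% larger than it need be, and about 1-6 points of power at 118 per arm.

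Those figures rest wholly on assumed AMAU inputs (20-50% of patients, mean stay 6-9 h, the ED coefficient of variation) and on a common SD in both arms. Under the wider assumptions in step 3 the loss may be close to nil. The direction is secure; the size is not. The change is still worth making because it costs almost nothing and replaces a rule that leaves the choice of covariates until the data are seen.

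**What to change.** For the primary outcome, replace the rule of adjusting for observed differences with one prespecified analysis that includes setting recorded at randomisation (ED or AMAU) as a fixed covariate. If the data are skewed, use a rank test stratified by setting, such as the van Elteren test. State that setting is fixed as at randomisation, so that a later move between units does not change a patient's category. Report the estimated effect separately for ED and AMAU.

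Use setting as a randomisation stratum only for allocations not yet generated. Recruitment began in November 2020 and was due to end in June 2021, so this may reach few patients or none. The covariate is the part that matters.

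The cost is one binary variable and a few sentences in the analysis section, settled before the data are examined. If setting at randomisation was not recorded as its own field, it would have to be recovered from enrolment or hospital records.
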